### Methods: participants, interventions, and outcomes

#### Study setting and eligibility criteria of the participating ICUs

An invitation to participate in the HELLO RCT, along with two reminders, was sent to all ESICM affiliates. Responses indicating interest in the trial were received from 679 individuals working in 679 centers. The respondents were asked to:Identify a nurse–physician dyad who would act as local investigators for the trial.Complete a form detailing the characteristics of their ICU.Organize a unit-level meeting to provide information about the trial, including the type of intervention, the study timeline, and the nature of the data to be collected.Attend one of three videoconferences (or watch the recording) that provided information on the study design, the HELLO bundle, the burnout instrument, and associated questions.Obtain IRB approval and inform the local research department at each hospital.

Among the 679 centers that expressed interest in the trial, 434 completed the first four commitments and were subsequently randomized into either the intervention group (*n* = 217) or the control group (*n* = 217). Table 2 and Fig. 1 list the 434 ICUs that were randomized. As shown in Fig. 2, participation in the trial is contingent upon obtaining IRB approval, hence, we anticipated more centers than the 146 needed based on the sample calculation to avoid being underpowered.

**Table 2 Tab2:** Participating countries

Region	Number of sites	Region	Number of sites
*Africa* • Egypt 9 • Ethiopia 4 • Ghana 2 • Libya 2 • Morocco 9 • Nigeria 3 • South Africa 1 • Tanzania 1 • Tunisia 4 • Uganda 1	33	*Southern Europe* • Bosnia and Herzegovina 2 • Croatia 7 • Greece 20 • Italy 23 • North Macedonia 1 • Portugal 17 • Serbia 2 • Slovenia 3 • Spain 37 • Turkey 29	141
*Asia* • Bangladesh 5 • China 3 • India 44 • Malaysia 1 • Pakistan 5 • Philippines 1 • Singapore 2 • Taiwan 3 • Vietnam 1	65	*Middle East* • Bahrain 1 • Iran 1 • Iraq 2 • Israel 4 • Kuwait 3 • Saudi Arabia 13 • United Arab Emirates 7	31
*Northern Europe* • Denmark 1 • Estonia 1 • Ireland 6 • Lithuania 2 • United Kingdom 26	36	*North America* • Canada 2 • Dominican Republic 1 • Mexico 4 • Nicaragua 1 • Puerto Rico 1 • United States 10	19
*Western Europe* • Austria 6 • Belgium 2 • France 36 • Germany 6 • Switzerland 6	56	*Oceania* • Australia 2	2
*Eastern Europe* • Hungary 3 • Moldova 1 • Poland 4 • Romania 6 • Russian Federation 1 • Ukraine 3	18	*South and Central America* • Argentina 3 • Brazil 4 • Chile 4 • Colombia 4 • Ecuador 4 • Peru 3 • Uruguay 8 • Venezuela 1	31

**Fig. 1 Fig1:**
[figure not shown]
Map chart showing participating countries across geographical regions

**Fig. 2 Fig2:**
[figure not shown]
HELLO cluster randomized controlled trial flowchart procedures and timeline

#### Modalities of informed consent

Healthcare professionals (HCPs) participating in this trial must agree to be part of the study and consent to having their data published once they log into the REDCap file, which will collect the Maslach Burnout Inventory (MBI), secondary outcomes, and demographic data. Additionally, some countries may require individual informed consent to be signed by each HCP prior to trial participation.

### Intervention

#### Explanation for the choice of comparators

This study compares intervention clusters to waitlist control clusters. We relied on a central randomization to select which clusters receive the intervention now and which are assigned to a waitlist to receive the intervention after the RCT concludes, in January 2025. Through utilizing a waitlist design, we expect that placebo effects will be effectively balanced between groups, as the control group’s knowledge of soon receiving a supportive intervention may yield improvements in their outcomes [33].

#### Intervention description

Intervention clusters will implement the HELLO bundle for four weeks, starting Monday, October 14, 2024. Twenty posters will be displayed in various locations within the ICU, including workstations, dressing rooms, and toilets. These posters, designed by the ESICM steering committee, will be shipped to all participating centers in either August (for the intervention group) or January (for the control, waitlist centers). The blue posters feature the term "HELLO" in different languages, the HELLO logo with a smiley face for the letter "O", and the ESICM logo.

Every Monday and Friday during the four-week intervention, the study's ESICM coordinators will send emails to the HELLO dyad at each participating center, highlighting the impact of positive psychology, team cohesion, and communication on healthcare professionals' (HCPs) well-being. These emails will then be forwarded to all HCPs via email, WhatsApp, or any other channel, and may also be displayed in the ICU by the local dyad. Saying "HELLO" before any huddles, handovers, or staff meetings will be encouraged.

Two HELLO jars/boxes will be placed in the ICU, designed by ESICM and sent to the centers. HCPs will be invited to write and insert positive messages about their colleagues and their work experience in the ICU into these jars/boxes. These messages will be accessible to anyone in the ICU who wishes to read them. At least twice a week, the HELLO dyad (or the head nurse and the department chief) will visit the ICU to greet everyone, set an example, explain the study, and share their reasons for participating in the trial.

Lastly, two paperboards will be displayed and updated as needed. These boards can include direct messages, stickers, drawings, photos, or any positive notes directed to other HCPs or the entire ICU.

In the ICUs from the intervention cluster, ESICM officers will make contact once a week to assess a rough estimate of the intervention's dosage. Each of the six components will be scored from 0 to 4, as illustrated in Table 3.

**Table 3 Tab3:** Adhesion score to measure the rate of implementation of the HELLO intervention

Adhesion score	0	1	2	3	4	+ 1
Number of Hello posters displayed (over 4 weeks)	None	< 5	5–10	10–15	> 15	More poster printed and displayed
Email reminders	Never forwarded	Forwarded only one week	Forwarded only two weeks	Forwarded only three weeks	Forwarded all the four weeks	Emails printed and displayed in the ICU
Hello during the Morning Huddles	Never	Rarely	Sometimes	Almost all the time	Always	Hello also introduced in other ICU meetings
Number of messages in the two Hello Jars	< 5	5–10	10–20	20–30	30–50	> 50
Lead by Example	Nurse and/or Physician never appeared in the ICU to say hello and promote the study	Nurse and/or Physician of the dyad came the first week to say hello and promote the study	Nurse and/or Physician of the dyad came the first two weeks to say hello and promote the study	Nurse and/or Physician of the dyad came the first three weeks to say hello and promote the study	Nurse and/or Physician of the dyad came all the four weeks to say hello and promote the study	Nurse and physician of the dyad set up specific meetings to explain and promote the study and took advantage of the study to promote well-being, team cohesion and communication
Number of messages in the two Hello Boards	< 5	5–10	10–20	20–30	30–50	> 50

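### The Lead by Example row of the adhesion score does not match the visit schedule: half the required visits can score 4 out of 4, and some permitted visitors and visit weeks have no level

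*Protocol article*

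**What the plan says.** All of the relevant text is in the protocol article.

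The Intervention description fixes the dose of the leadership component: "At least twice a week, the HELLO dyad (or the head nurse and the department chief) will visit the ICU to greet everyone". It names two sets of permitted visitors. One is the dyad, introduced under Study setting and eligibility criteria as the nurse–physician "dyad who would act as local investigators for the trial". The other, given in the parenthesis, is the head nurse with the department chief.

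Table 3 is captioned "Adhesion score to measure the rate of implementation of the HELLO intervention". Each of the six components is scored 0 to 4, with a further +1 column. In the Lead by Example row, level 3 is "Nurse and/or Physician of the dyad came the first three weeks to say hello and promote the study" and level 4 is "Nurse and/or Physician of the dyad came all the four weeks to say hello and promote the study". Levels 1 and 2 follow the pattern of level 3, for the first week and the first two weeks. No level gives a number of visits per week.

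Emails go out "Every Monday and Friday during the four-week intervention", which is also twice a week. Level 3 of the email row is "Forwarded only three weeks" and level 4 is "Forwarded all the four weeks".

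The article describes the score as an approximate measure of dose, obtained at a weekly contact with each intervention ICU. Under Statistical methods, the effect of adherence on outcome is to be reported by quartile of adherence. The primary analysis is by intention to treat, with allocated arm as a binary exposure.

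**The concern.** The component is defined by frequency and by who visits. The row that scores it ignores frequency, names only some of the permitted visitors, and gives partial delivery a level only when the visits fall at the start.

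Three things follow. An ICU making half the required visits can receive full marks. An ICU that delivers the component as the text allows, through its head nurse and department chief, may match no positive level. An ICU that starts a week late cannot be coded at all, so the contacting officer has to improvise.

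What is at stake is the adherence-by-quartile report. Quartiles depend on the ordering of ICUs, and this row can place less delivery above more.

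**Working it through.** The plan gives no worked figure for this score, so there is none to reproduce. The check sets the schedule against the row.

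**Inputs.** At least 2 visits per week for 4 weeks (Intervention description). Levels 0 to 4 by weeks visited (Table 3). Six components with 4 base points each: 6 × 4 = 24.

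**Required dose.** 2 × 4 = 8 visits, as a minimum. One visit a week gives 4, and 4/8 = 50%, so at most half the requirement. Two visits a week for three weeks give 6, and 6/8 = 75%.

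**Scoring rules compared.** Let a be the number of weeks with exactly one visit and b the number with two or more, counting at most two visits in any week.

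- Table 3, where the pattern has a level: score = a + b.
- A count out of 8, two visits per point, rounded up: score = ceil((a + 2b)/2) = b + ceil(a/2).
- Difference: a − ceil(a/2) = floor(a/2). This is 0 for a = 0 or 1, 1 for a = 2 or 3, and 2 for a = 4.

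| Visit pattern | Visits counted | Table 3 | Count out of 8 | Difference |
|---|---|---|---|---|
| Twice a week, four weeks | 8 | 4 | 4 | 0 |
| Once a week, four weeks | 4 | 4 | 2 | 2 |
| Twice a week, first three weeks | 6 | 3 | 3 | 0 |
| Once a week, first three weeks | 3 | 3 | 2 | 1 |
| Twice a week, weeks 2 to 4 | 6 | no level | 3 | not defined |
| Twice a week, four weeks, by a head nurse and chief who are not the dyad | 8 | none of levels 1–4 | 4 | not defined |

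Rows 2 and 3 show the reversal: 4 visits score above 6. Both patterns have a literal level, so no interpretation is needed.

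**Span of each level.** With at most two visits counted per week, level 1 covers 1–2 visits, level 2 covers 2–4, level 3 covers 3–6 and level 4 covers 4–8. The top level cannot separate half of the minimum from all of it.

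**Weeks without a level.** Each week is either visited or not, giving 2 × 2 × 2 × 2 = 16 patterns. The row has words for five: no week, the first, the first two, the first three, and all four. The other 11 have none.

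**Size.** The largest overstatement is 2 points: 2/24 = 8.3% of the base score. If the +1 column is counted, the total is 6 × 5 = 30 and the share is 2/30 = 6.7%.

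**Emails.** The schedule is 2 × 4 = 8. If a week counts only when both emails were forwarded, level 4 means 8 of 8 and half delivery cannot reach it. If one email is enough, the email row behaves like the visit row. Table 3 does not say which.

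**The case against.** The strongest reply is that this is a deliberately coarse scale. Officers contact sites once a week, the article claims only an approximate dose, and one point per week is a natural coding. Any five-level scale merges different doses; the count proposed here also gives 4 to both 7 and 8 visits. Weeks sustained may be as good a measure of a behavioural prompt as total visits, and nothing in the article ranks six visits in three weeks above four visits spread over four.

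Part of this stands. Coarseness is acceptable, and the overstatement above is a distance from a count rule, not from a validated dose. But the standard behind that rule is the article's own twice-weekly requirement. A top level met by half of that requirement does not measure whether it was kept. Coarseness also does not explain why permitted visitors and later weeks have no level.

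The visitor gap may affect few ICUs. The article does not say how often the head nurse and chief are not the dyad, and level 0 is worded without reference to the dyad, so the row is not consistent in excluding others. The gap in levels 1 to 4 remains.

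A reader might also infer that the email row has the same fault, so that once-weekly delivery of both components scores 8 of 8 against 6 of 8 for twice-weekly delivery over three weeks, with up to 4 of 24 points (17%) overstated. The document does not establish this. The email levels can fairly be read as the Monday and Friday schedule kept in each week counted. The two-item reversal and the 17% need the other reading.

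**Conclusion.** The point holds for the Lead by Example row and is minor. As printed, the row gives full marks for 4 of at least 8 required visits, ranks that above 6 visits in the first three weeks, gives no credit at levels 1 to 4 to visitors the text permits, and has no level for 11 of 16 weekly patterns. Against a capped count, the item is overstated by 0 to 2 points wherever the row gives a level, at most 8% of the 24 base points.

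This rests on two assumptions: that the twice-weekly requirement is the standard the score should reflect, and that the quartiles of adherence are formed from the Table 3 score. Statistical methods does not name Table 3, but it is the only adherence measure the article describes.

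A reader might go on to infer that a known share of ICUs would fall in the wrong quartile, or that the trial's main result is at risk. Neither follows. The article gives no distribution of total scores, so the number of ICUs changing quartile cannot be derived. The primary comparison uses allocated arm, not adherence, and is unaffected. For emails, the finding is ambiguity only.

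**What to change.** Reword the Lead by Example row as a count out of 8, crediting at most two visits per week: 0 = none, 1 = 1–2, 2 = 3–4, 3 = 5–6, 4 = 7–8. Credit visits by every role the Intervention description allows, and drop the restriction to the opening weeks. ICUs whose dyad visits twice a week in the first k weeks, or in all four, keep their present score of k. Eight visits crowded into week 1 count as 2 and score 1, as now.

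For emails, state that a week counts only if both were forwarded, or use the same count.

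The cost is one or two reworded table rows. Sites would report one or two simple counts at the weekly contact already planned, which is a small added burden.

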### Trial design

We designed a cluster RCT with a parallel design and 1:1 allocation ratio to evaluate the effectiveness of the HELLO bundle compared to a waitlist control group among at least 73 clusters of an average of 50 ICU-HCPs. Clusters will be matched based on ICU size (fewer or more than 20 beds) and country.

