#### Sample size

Statistical analysis will compare outcomes between intervention and control groups, aiming to demonstrate a reduction in the prevalence of burnout from 39 to 30%, assuming an intra-class coefficient of 0.15, and aiming for a statistical power of 80% (Fig. 3). Intra-class coefficient for the outcome variable was approximated and liberal when compared to precedent cluster trials performed on burnout performed in other context [34].

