**Fig. 3 Fig3:**
[figure not shown]
Sample size estimation assuming 50 respondents per cluster, a reduction in the prevalence of burnout from 39 to 30%, assuming an intra-class coefficient of 0.15 (base intra-class coefficient, range 0.1–0.2)

Primary and secondary analyses will be performed at an individual level adjusting for clustering. No imputation will be performed for missing variables.

Subgroup analyses will be conducted to explore potential moderators of intervention effectiveness.

Assuming an intra-class correlation of 0.15, 146 centers and 50 respondents per center, the study would allow to demonstrate a reduction in burnout prevalence from 39 to 30% with a statistical power of 80%. This study will enroll at least *k* = 73 clusters of 50 participants in average, totaling approximately *n* = 7300 participants (assuming an average cluster size of *m* = 50). The sample size was determined by power calculations from previous cross sectional studies [3, 7, 35, 36]. Based on estimated effect sizes, ICCs, and SDs of the outcome in the population from previous data, and accounting for attrition related to failure to obtain IRB or local research committees approval, we estimated that at least *k* = 73 clusters and *n* = 7300 participants would be sufficient to detect significant effects with 80% power in the primary outcome. However, because there was an uncertainty about the proportion of IRB and local research committees’ failure, as well as the number of ICUs finally not willing to participate to the trial, we included all the 434 ICUs (217 per group) who applied to the IRB before July 1st, 2024.

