### Statistical methods

#### Primary and secondary outcomes

Data will be described as median and interquartile range (IQR) or number and percentage. Categorical variables will be compared using Fisher's exact test and continuous variables using the nonparametric Wilcoxon test, Mann–Whitney test, or Kruskal–Wallis test.

The primary method of analysis will be a generalized linear mixed-effects model, which will be adjusted for cluster. We will use an intention-to-treat approach with a binary exposure variable indicating if the participant was randomized to the intervention or control group.

Predefined subgroup analyses will include:Center and country effect as assessed using mixed effect model. Briefly, we will assessed effect of the intervention while accounting for center and country effect. Center and country will be examined in dedicated mixed effect model and will be added as random effect on the intercept. Impact of the intervention will be reported when adjusted for these confounders. Center and country effect will be reported [37]. To test for the significance of center and country effects on outcome, we will use permutation tests [38]. Difference in rate of burnout will across centers and countries will be reported as median odds-ratio with their confidence interval. Influence of centers and country will be plotted.In addition, influence of adherence to protocol will be assessed. Impact of adherence on outcome will be reported by quartile of adherence.Last, influence of the job of respondents will be assessed.

If any additional exploratory or sensitivity analyses should be performed, they will be reported in the manuscript as post hoc analyses and interpreted as exploratory hypothesis generating analyses.

We will use an appropriate bootstrapping method with an identity link. We will use two-tailed tests for all models with statistical significance thresholds of 0.05. Results will be reported as mean difference, incidence rate ratio or odds ratios as appropriate.

Statistical analyses will be performed with R statistical software, version 3.4.3 (available online at http://www.r-project.org/) and packages ‘lme4’,and’lmerTest’. A *p* value < 0.05 will be considered significant.

Results will be reported in adherence with standards for reporting implementation studies of complex interventions guidelines [39].

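### Promoting the study is a scored, intervention-only activity just before the voluntary survey that supplies the primary outcome, so who answers may differ by arm in a way related to burnout, in an unknown direction

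*Protocol article*

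**What the plan says.** All places are in the protocol article.

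- **Intervention description:** at least twice a week, the dyad (or the head nurse and department chief) "will visit the ICU to greet everyone, set an example, explain the study, and share their reasons for participating in the trial". ESICM officers also contact intervention ICUs weekly to score adherence.
- **Table 3, Lead by Example:** levels 1 to 4 count the weeks in which a dyad member came to greet staff and promote the study. Level 4 reads "Nurse and/or Physician of the dyad came all the four weeks to say hello and promote the study". An extra point is given for dedicated meetings to explain and promote the study.
- **Explanation for the choice of comparators:** controls wait until January 2025. The waitlist is said to balance placebo effects.
- **Study setting and eligibility:** before randomisation, every ICU named a dyad and held a unit-level information meeting.
- **Participant timeline, Table 4 and Ethics:** both arms complete the MBI in September and November 2024. Consent is taken at each survey, from anyone who opens the link and agrees. Participation is voluntary.
- **Allocation section:** blinding is not possible.
- **Sample size:** the target is 50 respondents per ICU. No expected response rate or count of eligible staff is given. The section adds "No imputation will be performed for missing variables".

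**The concern.** The primary analysis set is not fixed at randomisation. It forms in November from staff who choose to answer, after four weeks in which one arm has repeatedly been told about the study by its leaders and the other, as far as the article describes, has not. Staff know their arm. Enthusiasts may be drawn in and cynical colleagues put off, or visible attention to burnout may prompt the most affected to respond. Either would shift the observed proportion with no change in true burnout.

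This concerns who answers, not how respondents rate themselves, so the waitlist argument about placebo effects does not cover it. Intention-to-treat and the mixed model apply only to respondents. Imputation is beside the point: someone who never opens the link has no record to impute. Without a denominator, a reader could not judge how far response differed between arms.

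**Working it through.** **Plan's own figure.** The inputs are in Sample size ("aiming to demonstrate a reduction in the prevalence of burnout from 39 to 30"%; "Assuming an intra-class correlation of 0.15, 146 centers and 50 respondents per center"; 80% power), Trial design ("parallel design and 1:1 allocation ratio") and Statistical methods ("We will use two-tailed tests for all models with statistical significance thresholds of 0.05").

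- Individually randomised size, two proportions, pooled variance, no continuity correction: 437 per arm.
- Design effect: 1 + (50 − 1) × 0.15 = 8.35.
- 437 × 8.35 = 3,649 per arm; 3,649 / 50 = 72.98, so 73 ICUs per arm, 146 in all, 7,300 people. Power is 80.0%. The stated figure reproduces.

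**Selection model.** Let p be true burnout in an arm, and r_b and r_n the response probabilities of burnt-out and other staff. Then

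observed prevalence = p·r_b / (p·r_b + (1 − p)·r_n),

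so observed odds = true odds × (r_b / r_n). Two consequences follow. A response rate that differs by arm does no harm if r_b / r_n is the same in both arms. If that ratio differs by arm, the crude odds ratio is multiplied by the discrepancy.

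**Assumptions (not in the documents).** p = 0.39 in both arms, so there is no true effect; control response is unrelated to burnout; R = r_n / r_b in the intervention arm. Worked case, R = 1.2: 0.39 / (0.39 + 0.61 × 1.2) = 0.39 / 1.122 = 34.8%.

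The last two columns give the chance of a significant false benefit (normal approximation, ICC 0.15, 50 respondents per ICU).

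| R | Observed, intervention | Spurious benefit | 73 ICUs per arm | 217 ICUs per arm |
|---|---|---|---|---|
| 1.1 | 36.8% | 2.2 points | 10% | 22% |
| 1.2 | 34.8% | 4.2 points | 25% | 61% |
| 1.3 | 33.0% | 6.0 points | 46% | 89% |
| 1.4 | 31.3% | 7.7 points | 66% | 98% |
| 1.49 | 30.0% | 9.0 points | 80% | above 99% |

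The last row solves for the planned effect: R = (0.39/0.61) / (0.30/0.70) = 1.49. The 217 column applies only if every randomised ICU takes part. More ICUs do not shrink the bias; they make it likelier to reach significance.

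**What R = 1.49 would look like.** If controls and burnt-out intervention staff respond at 50%, other intervention staff must respond at about 75% (0.50 × 1.49). Overall intervention response is then 0.39 × 0.50 + 0.61 × 0.746 = 65%, against 50% in controls. Roster counts would show a gap of that size.

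**Opposite direction.** With R = 1/1.2 and no true effect: 0.39 × 1.2 / (0.39 × 1.2 + 0.61) = 0.468 / 1.078 = 43.4%, an apparent harm of 4.4 points. With a true 30% in the intervention arm, R = 1/1.2 shows 34.0%, so a real 9-point benefit appears as 5 points. R = 1/1.49 shows 39% and hides it entirely.

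**The case against.** The strongest reply is that promoting the study is not the same as promoting the survey. Nothing in the article says that the visits invite or remind staff to complete the November MBI, and the emails are described as being about positive psychology, cohesion and communication. That stands: an effect on response is an inference. It is a reasonable one, since staff who keep hearing about a study from their leaders are placed differently when its survey arrives, but it is not stated.

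Second, controls are not untouched. They have a dyad, held the information meeting, and may use the investigator emails and slides listed under strategies to improve adherence. One sentence even sends the reminder emails to the dyad at each participating centre, although the abstract and component list treat them as part of the bundle. This also stands, so the point rests on the leader visits and their scoring, not on the emails.

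Third, a condensed article may leave invitation and reminder procedures to a fuller protocol. True, and their absence is not the finding. The finding is the stated imbalance: explaining and promoting the study is written into one arm's intervention and rewarded in its adherence score.

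Fourth, every sizeable bias above needs response to relate to burnout differently by arm, and matching the full effect needs strong selection in one arm only. That is correct, and it limits the conclusion to vulnerability, not demonstrated bias.

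**Conclusion.** The point holds as a design weakness that is cheap to reduce. The plan makes study promotion an intervention-only, scored activity immediately before a voluntary, unblinded survey, describes no comparable activity for controls in that period, and describes no denominator. Selective response could produce a spurious difference or hide a real one. Under the stated assumptions, a response ratio of 1.2 is worth about 4 points in either direction, against a planned effect of 9, and 1.49 is worth all of it. The ratios are illustrations, because the documents give no response rates.

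A reader might infer more than the documents support:

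- **That the bias favours the bundle.** The direction is not fixed by anything in the article.
- **That controls receive no study contact at all.** They share the dyad, the information meeting and possibly the team materials.
- **That response by arm cannot be calculated.** The article limits what REDCap records, but each ICU also completed a characteristics form whose contents are not shown. The supportable statement is that no denominator is described.
- **That the visits or emails recruit for the survey.** The article does not say so.

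**What to change.** 1. **Separate survey conduct from the campaign.** Reword Lead by Example and its Table 3 score to cover greeting and role modelling, and keep study and survey promotion out of the visits. Send both arms the same neutrally worded September and November invitations and reminders on the same dates.
2. **Record the denominator.** Have each dyad report the number of eligible HCPs at each survey, and report response by arm and job. This exposes a gap in response; it does not correct one.
3. **Conditional sensitivity analysis.** The Confidentiality section mentions a unique identifier, while the discontinuation criteria and Ethics sections call the study fully anonymous. Only if these can be reconciled, repeat the primary comparison in HCPs who also answered in September. Treat it as supportive: posters ship to intervention ICUs in August, so allocation may already be known at that survey, and the analysis does not remove differential non-response in November.

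The cost is common invitation templates, one staff count per ICU per survey, and possibly one extra analysis on a smaller linked sample. Items 1 and 2 do not depend on item 3, and the posters, huddles, jars and boards stay as they are.
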